## Results

The study was funded and peer reviewed by the National School for Social Security Loire department (École Nationale Supérieure de Sécurité Sociale) and the Conference for funders of prevention of autonomy loss for the elderly of the Loire department in November 2017, and obtained institutional review board approval in April 2018 by the committee for the protection of persons of Sud Est V of Grenoble University Hospital Center (registered under 18-CETA-01 No.ID RCB 2018-A00609-46). Data collection started in May 2018. The planned end date for data collection is May 2020. Data analysis will take place in the summer of 2020. First results are expected to be published in late 2020.

## Discussion

This study will enable us to determine whether a geriatric hotline offers effective management of elderly patients. Could planned hospitalizations be the best solution for our elderly? Will this approach lead to less geriatric syndromes [4-10]?

Wargon et al [4] demonstrated that the elderly spend more time in EDs, which is a potential source of dysfunction in the organization care offered by these services and lowers chances of positive outcomes for the patient. Therefore, there is interest in enabling the assessment of geriatric health status to limit visits to EDs as much as possible and improve the care pathways offered to elderly patients. In a retrospective study, Mazière et al [8] demonstrated that elderly admissions to EDs are independently associated with functional decline in terms of daily activities. The findings of these studies indicate that improving interactions between GP care and hospital services could enable more direct referrals of patients to multidisciplinary care in short-stay geriatric wards, consequently improving the functional prognosis of elderly patients and avoiding geriatric syndromes secondary to ED care.

The study has several strengths. It is a multicentric study covering a large patient sample. The diversity of the participating investigating centers (across three different regions) and their populations is also likely to offer diverse responses. Is the time spent in ED consultations greater in the larger centers? Does this lead to more cases of geriatric syndrome? Are there closer, more effective ties between GP clinics and hospitals in areas with a lower population density? Do these areas (with a lower population density) benefit from better understanding and communication of this type of care? The analysis will be conducted across subgroups (town by town) to avoid confusion bias. The overall population will be sourced from different types of regions (ie, rural, semiurban, urban) to reveal whether this factor has an impact on the knowledge of or access to the hotline [24]. The analysis will enable evaluation of GP clinic-hospital interactions [25] according to population centers, and the need for links between these health care areas, to determine the strengths and limitations and to reinforce GP clinic and hospital collaboration with the aim of reducing ED admissions [26].

By analyzing center by center, we will be able to describe each center with the different responses they offer. Ideally, this will help to improve the function of the geriatric hotline for the entire country and pave the way to new advances, especially in the organization of the care path in the long run.

The analysis also will be conducted in two sections. First, the call to the hotline will be analyzed. Did the experience of the doctor responding to the call influence the type of care recommended and the response offered? Does a high level of perceived emergency correlate to hospitalization via the ED? Is the hotline solely used by general medicine doctors? Would it be a good idea to roll out access to the hotline to other hospital specialties? Given the growing issue of population aging, the current geriatric services are not enough to care for all the elderly. This is why specialists are turning more toward other fields for geriatric assessment (eg, oncology, orthopedics). This study will reveal the different responses that can be provided by this tool (the hotline), from therapeutic or medical advice to referrals for hospitalization, ambulance call-outs, consultations, telemedicine, and more.

Second, we will study the profile of patients referred for hospitalization via the hotline to determine the characteristics of those the hotline recommends for admission to improve their health care approach. Does this tool lead to direct hospitalization in short-stay geriatric care for the less-fragile patients who still have some autonomy? Are the motives for admission less serious? We hypothesize that the mean duration of hospitalization will be shorter in cases in which it is planned, which leads to the question of whether the future of hospitalization is influenced by the ways patients are admitted. In their study involving 520 patients, Dijon et al [27] demonstrated that the intrahospital care pathways of geriatric patients referred directly to short-stay geriatric care are shorter and more effective than those experienced by patients who first went through EDs, with significantly shorter mean hospitalizations achieved through direct hotline-referred admissions (11.6 days versus 14.1 days with ED consultation; *P*<.05). Patients admitted to short-stay care via EDs were also the quickest to be rehospitalized in the future.

Another advantage of our study is its innovative character because there are currently very few studies analyzing geriatric hotlines [25]. In addition, it is observational in nature, which enables many types of procedures from across the country to be analyzed, leading to more standardized approaches.

The study does have limitations, notably its nonrandomized nature. There is no comparison because it is a descriptive study. The quality of the responses will be operator-dependent. Eventually, the goal will be to conduct a second study aiming to compare profiles of elderly patients hospitalized in short-stay geriatric wards via EDs versus those referred via a geriatric hotline. Through the first questionnaire, we will analyze the different responses provided by the hotline (eg, call-outs, consultations, telemedicine, day hospital). We will evaluate the number of hospitalizations avoided or deferred in time following the use of the hotline to reduce inappropriate passage through EDs.

This first study will demonstrate if managing patients by means of a geriatric hotline offers the most effective approach and results in shorter mean hospitalization durations and thus fewer complications and geriatric syndromes and fewer trips to EDs. It will also describe and compare the function of different geriatric hotlines across France to improve health care pathways for the elderly and pave the way toward future advances, such as new modalities of patient management, the development of more appropriate responses to this population, and the reduction of inappropriate visits to emergencies, which we know can be deleterious for the elderly.

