**Methods:**

The study will be conducted over 24 months in seven French university hospital centers. It will include all patients aged 75 and older, living in their own homes or nursing homes, who are admitted to short-stay geriatric wards following hotline consultation. Two questionnaires will be filled out by medical staff at specific time points: (1) after conducting the telephone consultation and (2) on admitting the patient to a short-stay geriatric medical care. The primary endpoint will be mean hospitalization duration. The secondary endpoints will be intrahospital mortality rate, the characteristics of patients admitted via the hotline, and the types of questions asked and responses given via the hotline.

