### Participants

The study population will be people aged 75 years and older, living in their own home or a care facility (including independent-living facilities), hospitalized in short-stay geriatric care and referred by the hotline in one of the investigating centers. All participants will be fully aware of the study and their rights regarding their participation. All participating patients will give their consent. Participants or a legally authorized representative will receive informational brochures and give their informed oral consent (more visual difficulties and writing for the elderly). All participants will be able, at any moment and by any method, to withdraw from the study.

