### Selection and Exclusion of Participants From Study

The inclusion criteria will be patients aged 75 years and older, male or female, living in their own home or a care facility (including independent-living facilities), hospitalized in short-stay geriatric care, and with confirmed receipt of information on the study and their rights, as stipulated by articles L.1122-1 of the French public health code, by 57 of the “Informatique et Libertés” data protection act, and by MR-003 of the French data protection and civil liberties authority (CNIL). The exclusion criteria will be patients aged younger than 75 years or refusing to participate.

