### Recorded Variables and Source Data

The study data will be collected directly from the questionnaires as the study progresses. For the first questionnaire (context of calls and solutions proposed), filled out by the hotline geriatric specialist (Textbox 1), health and administrative information will be collected for the study. The health data collected will include the identification of both speakers on the call, patient age, reasons for calling, degree of emergency as perceived by the geriatric specialist and the calling doctor (evaluated by simple scale from 0 to 10; 0 being a null degree of urgency and 10 an absolute urgency), and the responses offered by the geriatric specialist. The administrative data will include call duration (in minutes).

This questionnaire will be anonymous with no identifying criteria. It will be filled out every time contact is made via the hotline, irrespective of what responses are offered by the doctor (referrals to short-stay geriatric care or not).

For the second questionnaire, filled out by the geriatric specialist treating the patient during their hospitalization in short-stay geriatric care following referral from the hotline (Textbox 2), the sociodemographic, health, family, living situation, and location information will be collected for the study.

Sociodemographic data will include the first and last name of the patient, Patient Permanent Identification number, and patient age. These data will be anonymized on entry.

The health data collected will be the reason for hospitalization; number of hospitalizations during the past year; polypharmacy (four or more medications at the same time); biological data [17], including albumin and C-reactive protein levels for assessing nutritional status; and Charlson Comorbidity Index calculation using patient history for assessing the comorbidities of our geriatric population [18-20]; evaluation of activities of daily living (ADL) before hospitalization according to the validated ADL (/6) [21] and instrumental ADL scales (/4) [22]; evaluation of cognitive status using the Mini-Mental State Examination score (/30) [23]; and recommended referral after hospital discharge.

We chose the Charlson Comorbidity Index because it is a validated, reproducible, and simple comorbidity score that measures the impact of age (as there is excess mortality according to age), weighting by age from 1 (50-59 years) to 5 (90-99 years). This score is widely used for geriatrics publications.

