Family or marital status data will include single or with a partner, and with or without children. The living situation data will be the residence of the patient (own home, independent-living facility, nursing home). Type of living area will be urban, semiurban, or rural.

Context of calls and solutions proposed.

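### The data described cannot on their own show whether rural, semiurban or urban setting affects access to the hotline or knowledge of it

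*Protocol article*

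**What the plan says.** The protocol article's Discussion counts the diversity of the centers among the study's strengths. It says that patients will be drawn from rural, semiurban and urban settings "to reveal whether this factor has an impact on the knowledge of or access to the hotline". The same paragraph asks whether less densely populated areas benefit from a better understanding of this type of care.

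The Methods describe who is observed and what is recorded:

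- **Population.** Under Participants, the patients are those "hospitalized in short-stay geriatric care and referred by the hotline in one of the investigating centers". The abstract likewise covers patients "who are admitted to short-stay geriatric wards following hotline consultation".
- **Area type.** Recorded Variables and Source Data describes it with the second questionnaire, which the ward geriatrician completes for patients admitted after hotline referral: "Type of living area will be urban, semiurban, or rural". It also appears in the textbox of participant characteristics.
- **Call form.** The first questionnaire is completed at every hotline contact. "The health data collected will include the identification of both speakers on the call, patient age, reasons for calling", followed by perceived urgency and the response offered; call duration is the administrative item. The form is stated to be anonymous.
- **Denominators.** Table 1 gives total residents per center, from 16,840 to 513,300, split neither by age nor by area type.
- **Analysis.** Statistical Analysis names comparisons by sex and type of discharge, analyses by center, and patient profiles. The Discussion states that the study has no comparison.

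**The concern.** To learn whether area affects access, one must compare people who reached the hotline with people who could have reached it, by area type. The study observes only the first group, and records their area type only once they are admitted. Among included patients access does not vary, because all of them had it. To learn about knowledge, one must ask doctors who may or may not know of the hotline; only doctors who called are seen.

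At stake is an interpretation. Because the article offers the mix of settings as a strength, the area distribution of admitted patients could be taken as evidence on access when it may largely describe where the catchment population lives.

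**Working it through.** **1. Who is included.** The list under Selection and Exclusion of Participants asks for age, residence and being "hospitalized in short-stay geriatric care, and with confirmed receipt of information on the study and their rights"; it does not repeat hotline referral. Participants, the abstract, the description of the second questionnaire and Statistical Analysis (which speaks of subjects included via the hotline) all make referral a condition. The omission does not create a non-hotline group.

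**2. What each source can contribute.**

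| Source | Who is covered | Area type described? | Knowledge of the hotline? |
|---|---|---|---|
| First questionnaire | Every hotline contact | No item listed; anonymous | No |
| Second questionnaire | Hotline patients who were admitted | Yes | No |
| Table 1 | Total residents per center | No | No |

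**3. What the area mix of admitted patients measures.** For area type *a*, write

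N(a) = P(a) × c(a) × h(a)

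where N is the number of hotline-admitted patients, P the number of residents aged 75 and older in the catchment, c the calls per resident, and h the admissions per call. The study observes only N by area type. Neither P, c nor h is described by area type.

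**4. Effect of the missing denominator.** The article gives no area shares, so the shares here are assumptions, with two area types for simplicity. The ratio of c × h between areas is

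(urban share of patients / urban share of catchment) / (rural share of patients / rural share of catchment)

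Assume 70% of patients are urban:

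- catchment 70% urban: (0.70/0.70) / (0.30/0.30) = 1.0
- catchment 50% urban: (0.70/0.50) / (0.30/0.50) = 1.40/0.60 = 2.33

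As a second illustration, assume 20% of patients are rural and compute rural to urban:

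| Rural share of catchment | Calculation | Ratio |
|---|---|---|
| 10% | (0.20/0.10) / (0.80/0.90) | 2.25 |
| 20% | (0.20/0.20) / (0.80/0.80) | 1.00 |
| 30% | (0.20/0.30) / (0.80/0.70) | 0.58 |
| 40% | (0.20/0.40) / (0.80/0.60) | 0.375 |

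The same study data fit better, equal or worse rural access, depending on a quantity that the study does not collect.

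**5. What remains if the denominator is supplied.** Census counts fix P, and N/P then gives c × h, the rate of hotline-mediated admission. It does not give c. Take the 20% rural row, where the combined ratio is 1.00. If the rural-to-urban ratio of admissions per call is 0.5, the implied call ratio is 1.00/0.5 = 2.0; if it is 2, the implied call ratio is 1.00/2 = 0.5. Without area on the call form these cannot be told apart.

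**6. Knowledge.** No item described on either questionnaire asks about it, and doctors who never call are not observed. Neither census counts nor a new area field changes that.

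**The case against.** The strongest reply is that the sentence is one clause in a Discussion. Access by area type is not the stated objective, an endpoint or a listed analysis; the nearest secondary endpoint, improving awareness, is not a comparison by area. No sample size or model rests on it. This stands, and it limits the weight of the point.

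A reader might infer that area and access cannot be studied at all from these data. The documents do not support that. The real catchment mix is a fixed quantity, and external census counts combined with the area type of admitted patients would give a crude rate of hotline-mediated admission without any change to a form. That is a proxy, for the reason in step 5.

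A center-level reading is also possible: calls are logged everywhere, analysis by center is planned, and Table 1 gives residents. Calls per resident across seven centers would be a crude ecological view of hotline use. But no such rate is stated as planned, Table 1 does not classify centers by area type or give residents aged 75 and older, and seven voluntary centers differ in much else.

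A reader might also conclude that the call form certainly has no area field. The article shows a condensed description, not the form, and it mentions identifying both speakers, which could in principle carry a practice location. Against this, the textbox shows only caller type and responder grade, and the form is said to have no identifying criteria. The fair statement is that no area item is listed.

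**Conclusion.** The concern holds in a limited form: the article claims that its mix of settings will show an effect of area on access and knowledge, and the data it describes cannot show this on their own. Knowledge among doctors is not measured. Access is confounded with catchment mix and with admission once a call is made; under the assumed shares, the same 70% urban patient mix corresponds to an urban-to-rural ratio of 1.0 or 2.33. With census counts, a crude hotline-admission rate by area type becomes estimable, but not access itself.

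This rests on the call form being as the article describes it and on no area denominator being planned; the 70%, 50% and other shares are illustrations, not estimates. It would be wrong to infer that the planned results are compromised: the primary endpoint and the listed secondary endpoints do not depend on this claim. It is a minor point that should be corrected because it bears on what the study may conclude.

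**What to change.** In either case, remove the reference to knowledge of the hotline and treat the related question about less densely populated areas in the same way. Then choose one of two routes.

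1. **Add the data.** Put one area field on the first questionnaire (urban, semiurban or rural, for the patient or the calling practice). Report call rates and hotline-admission rates per 1000 residents aged 75 and older by area type, with census counts for a defined catchment as denominators. The cost is one tick-box and the retrieval of public counts. Calls logged before the change will lack the field; since collection began in May 2018 and was planned to end in May 2020, the later the change, the less it yields.

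2. **Limit the claim.** If the form can no longer be changed, replace the sentence with one such as: *The area type of patients admitted through the hotline will be described by center; it will not be interpreted as evidence on access.* Any census-based admission rate should be labelled a crude proxy that also reflects admission once a call is made. The cost is a change of wording.

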## Appendix

Multimedia Appendix 1 Peer-reviewer report from Comite de Protection des Personnes Sud est V.

## Abbreviations

ADL: activities of daily living
ED: emergency department
GP: general practitioner
